### Enrollment/randomization

Patients presenting to and discharged from participating units are enrolled automatically. As a cluster, crossover trial, randomization was limited to which unit the intervention would be deployed to first. Unit nursing staff were invited to participate in online surveys by e-mail, with reminders through staff meetings; their participation is voluntary.

### Intervention

The integration of the BIT into the unit is not itself a research intervention. Institutional leadership planned to deploy one team as a demonstration project, and to scale it if successful. This provided an opportunity for rigorous evaluation of the team’s effectiveness. The BIT, a multidisciplinary team comprising a psychiatric-mental health advanced practice nurse and a clinical social worker, with psychiatrist consultation as needed, is a modified version of an established model at Yale New Haven Hospital [14]. The team proactively screens patients upon admission to the unit, utilizing a protocol which includes a comprehensive chart review and, if indicated, a brief interview, seeking to identify those patients who possess risk factors indicative of either a potential psychological barrier to their own clinical progress or a potential risk for exhibiting disruptive, aggressive, or self-injurious behavior during their hospitalization. Once identified, the team provides interventions aimed at mitigating these risks through a variety of patient-specific interventions, including:
Psychiatric consultation and recommendations for symptom managementBehavioral plans of care for nurse/patient interactionPsychosocial support and brief psychotherapeutic interventionCurbside consultation for any member of the patient’s healthcare teamPatient advocacy and care coordinationPsychiatric-specific disposition support, including both inpatient and outpatient psychiatric services.

The team also provides education and support to the patient care teams (nurses, physicians, and others) and assists non-psychiatric staff in the management of patients who require behavioral healthcare.

All patients on a unit when the BIT is present will be eligible for BIT services, including those who are already admitted when the team crosses into the unit. During a month when the BIT is not present on a unit, the care and management of patients is not supported with proactive screening and management. Unit staff have access to all psychiatric or behavioral care routinely available in usual care. To ensure continuity of care, patients who continue to require psychiatric support at the time the BIT rotates off the unit will continue to receive care equivalent to the usual care condition. It is anticipated that monthly rotations will occur for 10 to 12 months.

All unit staff will be exposed to the intervention throughout the study, although after the first month of the study only those staff on the unit initially randomized to the intervention will have been exposed. This provides an opportunity for a comparison between exposed and unexposed staff. We note that patients present on the unit during the time of crossover are exposed to both the intervention and the control conditions. To avoid crossover effects and eliminate the logistical challenges of changing any behavioral care provider team during the admission, patients are excluded if they are present on a unit during crossover. This does lead to some possibility of contamination, since the BIT may be present in a unit during a control condition. However, the BIT comprises just two providers who were given strict instructions to avoid such contamination and who were also provided with training on how to defer questions or requests that would have resulted in contamination.

### Data collection

Data are being collected for patients and for unit staff. Patient information is documented as a component of usual clinical care, and those data needed for this study will be extracted from the electronic health record (EHR). Data include demographics, documentation of patient disruptive behavior and associated medication administration, and patient length of stay. Disruptive behavior was not previously specifically defined as part of routine clinical care, and documentation in the clinical chart was variable. As part of the study, new documentation fields were added to the EHR to enable description (and subsequent extraction) of specific patient behaviors. Disruptive patient behavior will be documented, including physical behaviors (hit, kick, slapped, shoved, spit at, thrown objects, grabbed, bitten, or attacked), verbal behaviors (threatening, bullying, harassing, name calling, blaming, insulting, yelling, cursing, intimidation), and any clinical interventions that are implemented to control any violent behavior.

Data will be extracted from the EHR by an automated query. The query will be validated by manual cross-check of a subset of cases. Data will be identified using an encounter number, allowing for merging of data for individual patients from different sources. The data files generated by manual query will be stored on secure servers and will be merged into a single dataset for analysis by the statistical team.

Anonymous surveys will be used to measure staff perceptions of their ability to manage disruptive patient behavior as well as their experience with the BIT. The behavioral health survey previously used at the organization is a 10-item instrument that assesses staff perceptions of workplace violence and safety (Table 1). The 10-item scale was adapted from prior work by Loucks et al. [9] and Rutledge et al. [12], who have validated the Behavioral Health Care Competency Survey. The survey was evaluated for content validity for the current purpose. For this study, we have adapted these instruments to be administered to nursing staff on the two participating units at three different time points: prior to the study, following the first 1-month intervention period, and after the study period has been completed (see Fig. 1). The surveys will be conducted electronically using Research Electronic Data Capture (REDCap) [5]. REDCap allows for surveys completed by the same individuals to be linked while maintaining the anonymity of respondents by preventing access to the linkage tables held securely within the REDCap application.

**Table 1 Tab1:** Behavioral health survey to assess staff perceptions of workplace violence and safety

1. Have you encountered patients exhibiting disruptive, threatening, or acting out behavior?					
Yes					
No					
2. If yes, did their behavior in any way impact your ability to provide care?					
Yes					
No					
3. Please specify how care was impacted (select all that apply):					
Patient was non-compliant with care					
Took time away from care with other patients					
Disruptive to unit and other patients					
Patient was combative					
Other (please describe)					
4. In your current position, which of the following did you experience while caring for a patient exhibiting disruptive, threatening, or acting out behavior? (Select all that apply.)					
Physical (hit, kick, slapped, shoved, spit at, thrown objects, grabbed, bitten, or attacked)					
Verbal (threatening, bullying, harassing, name calling, blaming, insulting, yelling, cursing, intimidation)					
Elopement					
Central line manipulation related to substance abuse					
Suicidal ideation					
Self-injury					
Other (please describe)					
5. Did you experience any of the following because of caring for a patient exhibiting disruptive, threatening, or acting out behavior?					
	Never	Rarely	Sometimes	Often	Always
Fear for personal safety					
Fear for patient safety					
Situational anxiety					
A disruptive family member rather than a patient					
Decreased job satisfaction					
6. How comfortable are you with strategies in caring for patients exhibiting disruptive, threatening, or acting out behavior?					
Very comfortable					
Somewhat comfortable					
Neutral					
Somewhat uncomfortable					
Very uncomfortable					
7. What reporting structure do you utilize when you have experienced an event with a patient exhibiting disruptive, threatening, or acting out behavior? (Select all that apply.)					
Consult service					
Confidential online reporting system					
First report of injury					
Employee Assistance Program					
Involve the primary team					
Involve the one-up leader					
Do not report					
None of the above					
8. What has been the most beneficial training/support you have received in your current position at Vanderbilt to prepare you to provide care for patients exhibiting disruptive, threatening, or acting out behavior? (Please rank order.)					
Behavioral health and safety learning management education module					
De-escalation and trauma informed care education					
Unit-based education					
Psychiatric consult service					
9. What do you think would be helpful for ongoing bedside support in the care of patients exhibiting disruptive, threatening, or acting out behavior? (Please rank order.)					
Behavioral management techniques					
Safety restraints					
Therapeutic communication					
General education					
Other (please describe)					
10. On a scale of 0 to 10, where 0 is the lowest and 10 is the highest level, rate your level of confidence in caring for patients exhibiting disruptive, threatening, or acting out behavior on your unit.					

References: Adapted from Zicko et al. [15] and Loucks et al. [9]

### Primary outcomes

This study has two primary outcomes: (1) any documented interventions to manage disruptive, threatening, or acting out behavior, and (2) staff self-reported comfort with and ability to manage patients exhibiting disruptive, threatening, or acting out behavior. Documented evidence of intervention is defined as:
Violence controlInjurious behaviorAdministration, including as-needed administration, of the following medications for behavior management: quetiapine (Seroquel), alprazolam (Xanax), clonazepam (Klonopin), haloperidol (Haldol), lorazepam (Ativan), olanzapine (Zyprexa), risperidone (Risperdal), and ziprasidone (Geodon).

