**Discussion:**

This ongoing trial will provide evidence on the real-world effectiveness of a proactive behavioral intervention to prevent disruptive, threatening, or acting out events in adult hospitalized patients.

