### Secondary outcomes

Secondary outcomes include the occurrence of each intervention separately, sitter use, use of physical or chemical restraints, patient length of stay, and unit nursing staff turnover (Table 2).

**Table 2 Tab2:** Outcome measures and definitions

Outcome	Definition	How we measure

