***Primary***		
**Violence control measures utilized, or patient injurious behaviors reported**	Composite of violence control nursing intervention; PRN medication administration of quetiapine, alprazolam, clonazepam, haloperidol, lorazepam, olanzapine, risperidone, or ziprasidone for behavior management; or nursing problem of violence risk or injurious behavior	Extraction of nursing documentation and medication administration from the electronic health record
**Nurse comfort and confidence in their ability to manage patients exhibiting disruptive, threatening, or acting out behavior**	Staff perceptions of workplace violence/safety, as well as perceived confidence, comfort, and most helpful training/support received	A behavioral health survey administered via Research Electronic Data Capture (REDCap) prior to intervention, 1 month after intervention began, and at the conclusion of the intervention

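### The patient composite mixes staff responses, a risk label and injurious behavior, and recorded verbal behavior enters no listed patient outcome, so the composite alone cannot show that disruptive behavior was prevented

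*Protocol article*

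**What the plan says.** All references are to the protocol article.

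- **Aim.** The abstract's Discussion promises evidence on the "effectiveness of a proactive behavioral intervention to prevent disruptive, threatening, or acting out events in adult hospitalized patients". The main Discussion speaks of impact on such events. The hypothesis at the end of the Background is wider and covers both prevention and management.
- **Patient primary outcome.** Primary outcomes defines it as "any documented interventions to manage disruptive, threatening, or acting out behavior" and lists violence control, injurious behavior and administration of named drugs. Table 2 titles it "Violence control measures utilized, or patient injurious behaviors reported" and gives the last component as "or nursing problem of violence risk or injurious behavior".
- **Secondary outcomes.** "Secondary outcomes include the occurrence of each intervention separately, sitter use, use of physical or chemical restraints, patient length of stay", together with nursing turnover.
- **Behavior data.** Under Data collection, "new documentation fields were added to the EHR to enable description (and subsequent extraction) of specific patient behaviors". These cover "physical behaviors (hit, kick, slapped, shoved, spit at, thrown objects, grabbed, bitten, or attacked") and a matching list of verbal behaviors such as threats, harassment, yelling and intimidation.
- **Use of the data.** Presentation of the results obtains injurious behavior from record entries of biting, kicking, throwing and the like, and reports each component of the composite separately.
- **Effect size.** Power calculation takes a 17.5% prior-year rate of behavioral interventions and a 5% reduction in their use.

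**The concern.** Most of the composite records what staff did or how they labelled a patient. The Intervention section has the team write behavioral care plans, advise on symptom management, educate staff, and screen for patients at risk of disruptive behavior. Each of these can change a component of the composite without changing how patients behave.

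Take a patient who threatens staff. If the episode is handled through a behavioral plan and no listed response or label is charted, the patient is a non-event. If the same behavior is met with a listed as-needed drug, the patient is an event. In the other direction, a listed drug given on the team's advice, or a risk label prompted by its screening, counts against the team.

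What is at stake is the interpretation. A favorable result could reflect fewer events or a different response to the same events. A null result could hide a real fall in behavior offset by more labelling or medication. The study added fields that would help separate these cases, but the verbal part of them is not tied to any listed patient outcome.

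**Working it through.** The question is what the outcome measures, so the main check is a mapping. The arithmetic that follows is an illustration.

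**1. What each listed item records**

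| Item | Listed in | Records |
|---|---|---|
| Violence-control intervention | Primary outcomes; Table 2 | Staff action |
| Listed medication for behavior | Primary outcomes; Table 2 | Staff action |
| Violence risk | Table 2, joined with injurious behavior | Staff-assigned label |
| Injurious behavior | Primary outcomes on its own; Table 2 joined with violence risk | Patient behavior |
| Restraints, sitters | Table 2, secondary | Staff action |

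**2. Where the recorded behaviors go**

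- *Physical.* The acts named in Presentation of the results match those listed in Data collection. Physical behavior therefore reaches the composite, although the article does not say outright that the new fields are the source.
- *Verbal.* No patient outcome in Primary outcomes, Secondary outcomes, Table 2 or Presentation of the results names it. The staff survey (Table 1, item 4) asks nurses about verbal incidents, but that is staff recall at three time points and not a patient-level outcome.

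**3. Which reading of the 5% applies**

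Alpha is not stated, so two-sided 0.05 with 80% power is assumed. Per-arm size before clustering is n = (1.96 + 0.8416)² × [p1(1−p1) + p2(1−p2)] / (p1−p2)².

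- Absolute, 17.5% to 12.5%: 7.849 × 0.25375 / 0.0025 ≈ 797 per arm.
- Relative, 17.5% to 17.5 × 0.95 = 16.625%: 7.849 × 0.28299 / 0.00875² ≈ 29,000 per arm.

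The plan has 1790 patients in total, so only the absolute reading is credible. The 1790 itself is not at issue here.

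**4. How much change in response would mimic the target**

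Let s be the share of composite events that rest on staff response alone. The document does not give s. The relative fall in those responses that yields 5 points with behavior unchanged is f = 5 / (17.5 × s).

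| s | f |
|---|---|
| 1.0 | 5 / 17.5 = 28.6% |
| 0.8 | 5 / 14.0 = 35.7% |
| 0.6 | 5 / 10.5 = 47.6% |
| 0.5 | 5 / 8.75 = 57.1% |

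**5. The opposite direction**

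Suppose the team truly lowers the composite to 12.5%, leaving 87.5% of patients event-free. New violence-risk labels in 5 / 87.5 = 5.7% of those patients would bring the rate back to 17.5% and hide the effect. The labelling rate is likewise not given.

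**The case against.** The strongest defense has four parts.

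- **Behavior is already in the outcome and is reported separately.** This stands for physical acts. A reader might infer that the composite counts only staff response, or that none of the new fields feeds an outcome. The document does not support either reading: injurious behavior is a named component and has its own planned percentage. But Table 2, which defines the secondary outcomes, joins it with violence risk, and no component names verbal behavior. The passing mention of counts of behavioral problems under Treatment of outliers defines no outcome.
- **A threatening patient could enter through the violence-risk item.** This is possible. It depends on the label being charted, and the label marks risk rather than an observed act, so it does not show whether threats fell.
- **The hypothesis covers management as well as prevention.** This stands. Fewer control measures because a plan worked is a legitimate management benefit. A reader might infer that a favorable result would necessarily be misreported as prevention; the document supports only that it could be. The abstract's prevention wording does go further than the composite can carry alone.
- **Charting of behavior is unblinded and was variable before the study.** This stands, and it limits the remedy. Staff education in BIT months may raise charting of behavior, so the added outcome should be supportive. A rule that it must move in the same direction as the composite would be too rigid.

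The full protocol is not shown and may map the fields in more detail. The point rests on the outcome definitions that the article does state.

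**Conclusion.** The point holds as a matter of interpretation and is worth a cheap improvement. The composite mixes staff responses, a staff-assigned label and injurious behavior. The team acts directly on the first and may raise the second, so the composite could move either way without a change in behavior. Verbal behavior is recorded but named in no listed patient outcome, although threatening events are part of the question.

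The size is illustrative: a 57% to 29% fall in staff-only responses would give the full 5-point effect if such events are 50% to 100% of the 17.5%. The 29% end assumes that every event is staff-response only, which the document does not say. A reader might infer from a relative reading of the 5% that a shift of 0.9 points (0.05 × 17.5) would be enough. That reading is not credible at the planned size.

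**What to change.** Make these changes before the arms are compared, and date them. Enrollment has ended according to Trial status. If a comparison has already been made, label the outcome as added afterwards.

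1. Add to Table 2 a supportive secondary outcome: *any documented physical or verbal disruptive behavior*, drawn from the existing fields and kept separate from the violence-risk label. Report the physical and verbal parts as well.
2. Analyze it with the same model as the composite and give the estimate with a confidence interval.
3. Word a conclusion that rests on the composite alone as an effect on the use of behavioral interventions, or on management. Claim prevention of disruptive behavior only with support from the behavior outcome, and state that charting is unblinded and may increase in BIT months.
4. Reconcile the component lists at the same time. Primary outcomes counts medication including as-needed use, while Table 2 counts as-needed use only. Presentation of the results places restraints and sitters among violence-control measures, while Table 2 lists them as separate secondary outcomes.

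The cost is one more extraction from fields already built, one more outcome with its two parts to analyze, and a few sentences on interpretation. No new data collection is needed.

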### Secondary outcomes

Secondary outcomes include the occurrence of each intervention separately, sitter use, use of physical or chemical restraints, patient length of stay, and unit nursing staff turnover (Table 2).

**Table 2 Tab2:** Outcome measures and definitions

Outcome	Definition	How we measure
***Primary***		
**Violence control measures utilized, or patient injurious behaviors reported**	Composite of violence control nursing intervention; PRN medication administration of quetiapine, alprazolam, clonazepam, haloperidol, lorazepam, olanzapine, risperidone, or ziprasidone for behavior management; or nursing problem of violence risk or injurious behavior	Extraction of nursing documentation and medication administration from the electronic health record
**Nurse comfort and confidence in their ability to manage patients exhibiting disruptive, threatening, or acting out behavior**	Staff perceptions of workplace violence/safety, as well as perceived confidence, comfort, and most helpful training/support received	A behavioral health survey administered via Research Electronic Data Capture (REDCap) prior to intervention, 1 month after intervention began, and at the conclusion of the intervention

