### Presentation of the results

After completion of enrollment and data analysis, the results of the trial will be communicated to the public through manuscript publication and submission of the results to the ClinicalTrials.gov database. Submission for publication will include public access to the full study protocol and statistical code. Authorship will be based on the International Committee of Medical Journal Editors guidelines [6], and professional writers will not be used.

The flow of patients through the study will be presented in a flow diagram (Fig. 1). Baseline characteristics will be presented by treatment group, as shown in Table 2. The percent of patient injurious behaviors reported will be determined by extracting reports of biting, kicking, throwing, etc., from the EHR. The percentage of violence control measures used will be determined by extracting medications, restraints, and sitters ordered from the EHR.

A composite of all documented indications of disruptive patient behavior, including violence control nursing interventions, as-needed (PRN [*pro re nata*]) medication administration for behavior management, nursing problem of violence risk, or any injurious behavior, will be extracted from the EHR. Each component of the primary outcome will also be reported separately, along with documented physical restraints for disruptive patient behavior.

The percentage change in nurse comfort and confidence in their ability to manage patients exhibiting disruptive, threatening, or acting out behavior; in perceptions of workplace violence/safety; and in perceived confidence, comfort, and most helpful training/support received will be determined by comparing surveys conducted pre-implementation, 1 month after the intervention began, and post-implementation.

The rate of unit nursing staff retention will be determined by extracting rates from internal human resources records. Patient length of stay will be determined by extracting data from the EHR.

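### The primary composite counts a 'violence risk' nursing problem as an event, but identifying that risk is the BIT's task in intervention months only, so ascertainment may differ by arm

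*Protocol article*

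**What the plan says.** The protocol article defines the first primary outcome in three places.

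- **Primary outcomes section.** The outcome is "any documented interventions to manage disruptive, threatening, or acting out behavior". The list beneath has three items: violence control, injurious behavior, and administration of named medications. There is no risk item.
- **Table 2, Primary rows.** The composite is a violence-control nursing intervention, PRN use of the named medications for behavior management, or a "nursing problem of violence risk or injurious behavior".
- **Presentation of the results.** The composite again includes "nursing problem of violence risk, or any injurious behavior".

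Table 2 also lists the components as secondary outcomes. There, violence risk and injurious behavior form one joint component. The source is nursing documentation and medication administration in the electronic health record.

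On the intervention, the Intervention section says: "The team proactively screens patients upon admission to the unit". Among the things it looks for is "a potential risk for exhibiting disruptive, aggressive, or self-injurious behavior during their hospitalization". The team also gives nurses behavioral plans of care and educates unit staff. In months without the team there is no proactive screening.

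**The concern.** A violence-risk entry is a judgment about what a patient might do. It is neither an act nor an intervention to control one, so it does not fit the Primary outcomes definition. It is also close to what the BIT is there to produce, namely recognition of at-risk patients. Screening and staff education take place in intervention months only, and the staff who document know whether the team is present. How readily this component is recorded could therefore depend on the arm.

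If recognition of risk rises in BIT months while real acts and control measures fall, the two movements offset each other inside one yes/no outcome. A null primary result could then not be told apart from better risk detection. The planned component breakdown would not settle it, because the label and the act share a component. The 6-month interim look would not reveal it either, because it makes no comparison between groups.

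**Working it through.** **Step 1. Inputs.** From the Power calculation section: control rate 17.5%, a reduction of 5% (read as absolute, so 12.5% under the BIT), cluster size 90, both correlations 0.1 or about 0.1, total 1790 (895 per arm), power 80%. Not stated there and assumed here: two-sided alpha 0.05, the normal approximation with unpooled variance, and the usual cluster-crossover design effect 1 + (m − 1)ρ − mη.

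**Step 2. The plan's own figure.**
- Before clustering: n per arm = (1.960 + 0.842)² × (0.175 × 0.825 + 0.125 × 0.875) / 0.05² = 797, total 1593.
- With both correlations exactly 0.1: design effect = 1 + 89 × 0.1 − 90 × 0.1 = 0.9, total about 1434. This is not 1790.
- A total of 1790 at 80% power needs a design effect of about 1.12. I use 1.124, which corresponds to η = (9.9 − 1.124)/90 = 0.0975. That is compatible with the word 'about', but it is back-solved and does not stand in the protocol.

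**Step 3. Labels added in the BIT arm only.** Let f be the fraction of otherwise event-free BIT patients who become events through a violence-risk entry alone. The documents give no value for f, so a range is shown.

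- Observed BIT rate: q = 0.125 + f × 0.875
- Apparent reduction: d = 0.175 − q
- SE = √{1.124 × [0.175 × 0.825 + q(1 − q)] / 895}
- Power = Φ(d/SE − 1.960) + Φ(−d/SE − 1.960)

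| f | BIT patients affected (of 895) | q | d (points) | SE | Power, design effect 1.124 | Power, design effect 0.9 |
|---|---|---|---|---|---|---|
| 0% | 0 | 12.5% | 5.0 | 0.0179 | 80% | 88% |
| 1% | about 8 | 13.4% | 4.1 | 0.0181 | 63% | 72% |
| 3% | about 23 | 15.1% | 2.4 | 0.0185 | 25% | 30% |
| 5% | about 39 | 16.9% | 0.6 | 0.0189 | 6% | 7% |

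The apparent effect reaches zero at f = 0.05/0.875 = 5.7%, about 45 of 895 patients.

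**Step 4. The same labeling in both arms.** If the fraction f is added in control months too, the difference is (0.175 + 0.825f) − (0.125 + 0.875f) = 0.05 × (1 − f). At f = 5% that is 4.75 points, almost no dilution. The damage comes from labeling that differs by arm, not from the label as such.

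**The case against.** The strongest reply is that the mechanism is plausible but not documented. The team's listed outputs are consultation, care plans, support, curbside advice, advocacy and disposition help; entering a nursing problem is not among them. Unit staff do the charting, and by the Intervention section's own account all of them are exposed during the study. A learned habit of labeling could carry into control months, and Step 4 shows that an equal rise does little harm. Control-month nurses might even label more patients, because they meet more unmanaged behavior. This stands. A reader might infer that screening generates the labels and that the composite is biased against the BIT, but no passage says so.

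A second reply is that the shorter list in Primary outcomes may be shorthand, since its three items map one-to-one onto Table 2's three components. This also stands. The omission shows an inconsistency; it does not prove that the label is dispensable.

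A reader might extend the point to medication because the BIT offers "Psychiatric consultation and recommendations for symptom" management. That text names no drug, so the medication component is at most a reason for a supportive analysis.

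Third, the plan has partial safeguards. Components are reported, restraints and sitters are secondary outcomes, and Presentation of the results plans a percentage of injurious behaviors from reports of specific acts. A fall in actual acts could therefore be seen. The primary test itself stays exposed, and the joint component does not separate label from act.

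Finally, Trial status gives the end of enrollment as 30 December 2019. Deleting a component thought to count against the intervention after seeing results by arm would be an outcome change in its favor. That limits which repair is acceptable.

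**Conclusion.** The point holds as a weakness in how the primary composite is fixed. Two places count a violence-risk entry alone as an event, and the section that defines the outcome does not list it. The entry concerns the risk that the intervention is designed to identify, in one arm only. Ascertainment that depends on arm is a real possibility, and nothing in the article prevents a BIT-prompted entry from counting.

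Direction and size are not established. The figures of 4.1, 2.4 and 0.6 points, with power of about 63%, 25% and 6%, are illustrations. They rest on assumed values of f, no matching rise in control months, an absolute reading of the 5% reduction, two-sided 0.05, and a design effect back-solved to the stated power. They are not a forecast of the trial's power. They do show that a modest difference in labeling between arms would matter, because about 45 BIT patients would be enough to cancel the whole planned effect.

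**What to change.** 1. **Reconcile the three definitions** in Primary outcomes, Table 2 and Presentation of the results. If no between-arm comparison has yet been made, take violence risk out of the primary composite and record the date and reason. If one has been made, keep the primary as it is and add a sensitivity analysis, fully specified before it is run, that excludes patients whose only qualifying item is violence risk.
2. **In either case, split the joint component.** Extract violence risk and injurious behavior as separate items in the query and in Table 2's component list. Report the risk label by arm as a process measure.
3. **Add one supportive analysis** limited to violence-control intervention and injurious behavior.
4. **State whether the 17.5% planning rate included violence-risk entries.** The Power calculation section describes it as patients who required behavioral interventions, which leaves this open.

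While the definitions are being aligned, the medication wording should be settled too: Primary outcomes covers administration including as-needed use, while the other two places say PRN only.

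The cost is revised wording and a small change to the query. Separate extraction of the label cannot be taken as already in place, because Table 2 joins it with injurious behavior. If the label is removed, the composite event rate may be below 17.5%, and the planning rate would need restating.
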